### Randomization and blinding

All participants will be randomly allocated to the SLGD group, LLGD group, or control group based on a ratio of 1:1:1. The random number table will be generated by SPSS 19.0 for Windows software. A research assistant who will not participate in this clinical trial will send the random number table to the pharmaceutical company for packaging to maintain the blinding of participants and clinical investigators. According to the order of enrollment, the clinical investigators will assign the numbers in ascending order and the pharmacists will distribute the corresponding drug. Participants, clinical investigators, and statisticians will all be blinded until completion of the whole trial. The randomization list and blinding codes will be kept strictly confidential.

Based on the requirements of medical ethics, a double-blind study should set up an emergency letter for each blind number. Emergency letters will be sealed in opaque envelopes. The contents of the letter will include group details and emergency situations. Emergency letters should be sealed and can only be opened when necessary. The emergency letter will be read by clinical investigators in cases of severe AEs, in which knowing the experimental treatment is compulsory for further medical interventions. The case will be treated as a withdrawal and the clinical investigator will record the corresponding reason in the CRF. All emergency letters will be retrieved together with the CRF after the study. Double unblinding will be used in this trial. Briefly speaking, the first unblinding will uncover the codes of treatments, namely A, B, and C. After the completion of the statistical analysis, the second unblinding will uncover the specific drugs corresponding to the cords.

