## Methods/design

### Study design

The study protocol was approved by the Medical Ethics Committee of Longhua Hospital Affiliated to Shanghai University of Traditional Chinese Medicine (2017LCSY069) and registered in the Chinese Clinical Trial Registry (http://www.chictr.org.cn/edit.aspx?pid=24555&htm=4) with number ChiCTR1800014364 on 1 January 2018.

This study will be a 16-week, randomized, multi-center, double-blinded, three-arm, dose-optimization, placebo-controlled clinical trial. A total of 243 patients with NAFLD will be recruited through recruitment advertisements and introductions from doctors from three community healthcare centers in Shanghai, namely Zhangjiang community healthcare center, Beicai community healthcare center, and Sanlin community healthcare center. All three centers are based in Pudong New Area, Shanghai and no obvious difference will be supposed to exist in population and socioeconomic aspects. Eligible patients with NAFLD who agree to participate in the study will be randomly assigned to the standard dose Lingguizhugan decoction (SLGD) group, low dose Lingguizhugan decoction (LLGD) group, or the control group on a ratio of 1:1:1. On the basis of behavioral intervention therapy, patients in the SLGD and LLGD groups will be treated with different doses of LGZG; the control group will receive placebo. The LLGD group will be made of half of the standard dose, and the placebo will be one-tenth of the standard dose but with soluble starch, mixed colorant, and bitter component to achieve a comparable appearance, smell, and taste. The course of treatment will last 12 weeks. A 4-week follow-up will also be arranged to assess the continued effect. Participants will be assessed at week 0 (baseline), week 4, week 8, week 12 (end of treatment), and week 16 (end of follow-up). All participants will be asked to provide written informed consent before entering the trial. The study flow chart is shown in Fig. 1 and participant timeline is presented in Table 1. The Standard Protocol Items: Recommendations for Interventional Trials (SPIRIT) Checklist is presented in Additional file 1.

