### Statistical analysis

The analysis of efficacy and safety will be based on the principle of intention-to-treat (ITT), namely all randomized participants will enter the final analysis. The missing value will be filled by the method of the last observation carried forward. Data will be presented as mean with standard deviation, median with range, or number with percentage. Data analysis will use the SPSS 19.0 for Window software. All statistical inferences will be performed using a two-sided test with a statistically significant test level of *P* < 0.05 and the confidence interval of parameters will be estimated by 95% confidence interval. Differences within groups will be assessed by paired t-test, chi-square test, or Wilcoxon signed rank test according to specific variables. Differences between groups will be assessed by one-way analysis of variance or Kruskal–Wallis test based on characteristics of data. Post-hoc pairwise multiple comparisons will be performed if statistical significance is found.

No interim analysis was arranged in this trial due to a short intervention period and safety profiles of LGZG. Potential sub-group analyses will be determined based on characteristics of included participants, for instance, different categories of body mass index and different combined diseases.

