## Discussion

NAFLD is a widely health problem and > 80% of obese people suffer from NAFLD globally [36]. A large population-based study has demonstrated that NAFLD is one of the important causes of hepatocellular carcinoma (HCC) and the incidence of NAFLD-related HCC is increasing by approximately 10% per year [37]. However, the pathogenesis mechanism of NAFLD is vague [38]. There is still no drug currently approved for the treatment of NAFLD by the U.S. Food and Drug Administration (FDA) or the European Medicines Evaluation Agency (EMEA) [10, 39]. Hence, many patients with NAFLD will seek help from TCM interventions, especially Chinese herbal medicine.

Treatment based on pattern differentiation is the character of understanding and treating disease by TCM. Therefore, we introduce pattern differentiation as one of inclusion criteria for NAFLD participants, namely spleen-yang deficiency. LGZG is the corresponding formula for this pattern. Previous animal studies also indicated the potential efficacy of LGZG against NAFLD [20, 22]. A clinical trial will then be necessary to demonstrate the application. To our knowledge, our trial is the first multi-center, randomized, double-blinded, placebo-controlled clinical trial to assess the efficacy and safety of LGZG for NAFLD.

To ensure the quality of this research, a strict system of training and supervision will be established. Training sessions will be held for each center to explain the study protocol and potential upcoming matters. How to confirm the TCM pattern of spleen-yang deficiency and how to collect biological samples will also be explained in training sessions. The biochemical measurements of each participating center will be tested uniformly by KingMed Diagnositics (Shanghai) to guarantee the consistency. The ECG and liver-kidney echo ratio by ultrasound will be examined in the corresponding experimental center with uniform standard.

The results of this trial will provide initial evidence regarding the efficacy and safety of LGZG in the treatment of NAFLD with spleen-yang deficiency pattern. Biological samples collected in this trial may explain the possible action mechanisms of LGZG associated with oral and gut microbiota.

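### The between-group tests named in the protocol leave out centre, although the liver-kidney echo ratio is examined locally at each of three centres

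*Protocol article*

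**What the plan says.** - **Centres.** Study design names "three community healthcare centers in Shanghai, namely Zhangjiang community healthcare center, Beicai community healthcare center, and Sanlin community healthcare center". It assumes of them that "no obvious difference will be supposed to exist in population and socioeconomic aspects".
- **Allocation.** Randomization and blinding gives the ratio ("All participants will be randomly allocated to the SLGD group, LLGD group, or control group based on a ratio of 1:1:1") and the source of the list ("The random number table will be generated by SPSS 19.0 for Windows software"). It continues: "According to the order of enrollment, the clinical investigators will assign the numbers in ascending order and the pharmacists will distribute the corresponding drug". Stratification, blocking and separate lists by centre are mentioned neither as used nor as not used.
- **Measurement.** The Discussion treats two kinds of data differently. For laboratory data, "The biochemical measurements of each participating center will be tested uniformly", at one named laboratory. For imaging, "The ECG and liver-kidney echo ratio by ultrasound will be examined in the corresponding experimental center with uniform standard". No central reading is described.
- **Analysis.** Statistical analysis fixes the method: "Differences between groups will be assessed by one-way analysis of variance or Kruskal–Wallis test based on characteristics of data". The examples of possible subgroups are body mass index and combined diseases; centre is not among them.
- **Timing.** Trial status reports recruitment from July 2018 to February 2019 and data lock in June 2019.

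**The concern.** The only argument offered for treating the centres as interchangeable concerns who the patients are and where they live. How an outcome is obtained at each centre is a different matter. By sending all biochemistry to one laboratory, the protocol itself shows that it regards between-centre measurement as something to control. The liver-kidney echo ratio, the only imaging measure among the listed outcomes, does not have that protection beyond a common standard.

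With a one-way test, any difference between centres in the analysed outcome stays in the error term and lowers power. If the list was also not balanced by centre, one arm can by chance draw more of its patients from one centre, and the unadjusted contrast then carries part of the centre difference. A centre term removes both effects for little cost, and the tests as named have no place for one.

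**Working it through.** The plan gives no figure on this point to reproduce, so the check asks two things: how uneven the arms could be across centres, and what omitting centre costs.

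**Inputs from the protocol:** three arms at 1:1:1, 81 per arm, 243 in total, three centres, two-sided test at 0.05.

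**Assumptions, not in the protocol:** centre sizes, centre shifts, and the treatment effect used to illustrate power.

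**1. Spread of arms over centres if the list was not stratified.** Fix 81 per arm overall and let chance decide the split by centre. For a centre of 81, its share of the trial is p = 1/3. The SD of the difference between two arms in the share drawn from it is

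sqrt[ p(1 − p) × 243/242 × 2/81 ] = sqrt[ 0.2222 × 1.0041 × 0.02469 ] = 0.074, or 7.4 percentage points.

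A simulation of 100,000 allocations agrees (7.4 points; 95th percentile of the absolute difference about 15 points). The gap between the largest and smallest arm, at the centre where it is worst, is:

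| Assumed centre sizes | Median gap | 95th percentile | Chance of a gap of 10 or more |
|---|---|---|---|
| 81 / 81 / 81 | 9 | 16 | 50% |
| 162 / 54 / 27 | 8 | 14 | 34% |

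With permuted blocks of 6 within centre (two per arm in each block), the gap could not exceed 2.

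**2. What a gap does to one comparison.** A gap of 10 is 10/81 = 12 percentage points. If that centre differs by 0.5 SD, the contrast between the two arms moves by 0.12 × 0.5 = 0.06 SD. The standard error of that contrast is sqrt(2/81) = 0.16 SD. A typical gap is therefore a modest nuisance.

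**3. Power lost by leaving out centre.** Let equal-sized centres be shifted by −s, 0 and +s within-centre SDs on the analysed outcome. The between-centre variance is 2s²/3, so its share of the total is (2s²/3)/(1 + 2s²/3):

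- s = 0.25: 0.042/1.042 = 4%
- s = 0.5: 0.167/1.167 = 14%
- s = 1.0: 0.667/1.667 = 40%

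Take arm means of 0, 0.125 and 0.5 SD. Their squared deviations from the mean of 0.2083 sum to 0.1354, so the noncentrality with centre removed is 81 × 0.1354 = 10.97. Leaving centre in the error divides this by 1.042, 1.167 or 1.667, giving 10.53, 9.40 and 6.58. Simulated power (6,000 trials per setting) is:

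| s | Centre ignored | Centre in model |
|---|---|---|
| 0 | 85% | 85% |
| 0.25 | 84% | 85% |
| 0.5 | 79% | 85% |
| 1.0 | 62% | 85% |

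The noncentral F distribution with these values gives 84.7%, 83.1%, 78.4% and 62.1% with centre ignored, in agreement within simulation error.

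**4. Type I error.** With no treatment effect, rejection rates were 4.9% to 5.2% with centre ignored and 4.7% to 5.1% with centre in the model. Both hold the nominal level.

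**The case against.** **The unadjusted analysis is valid.** This stands. Randomisation protects the type I error, and chance imbalance across centres is already part of the standard error. The issue is precision.

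**A reader might infer that the list was not balanced by centre.** The article does not support that. It is silent on strata and blocks, ascending order of enrolment fits number ranges reserved for each centre just as well, and the full protocol (V3.0) is not shown. The figures on arm gaps are therefore conditional. The analysis part is firmer, because the one-way tests are named.

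**A reader might infer that the primary outcome is compromised.** It is not, as far as measurement goes. HOMA-IR and most secondary outcomes rest on biochemistry from one laboratory. The measurement argument falls mainly on one secondary outcome.

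**A reader might infer biased ultrasound readings.** The documents do not say that machines or readers differ. They provide a uniform standard, training at each centre, and blinding of participants and clinical investigators. Secondary outcomes are also evaluated from baseline to week 12, so a constant centre offset cancels in a change score if the patient is examined at the same centre both times. What would remain is a centre difference in the change itself, from scale or from local delivery of the lifestyle programme; both are inferences.

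**The larger power losses need implausible shifts.** This is fair for s = 1.0, where centre would carry 40% of the variance. The 4% to 14% range is the more useful guide, and at its low end the loss is about one percentage point.

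**Conclusion.** The point holds as an improvement in precision, and its importance is modest. The named between-group tests omit centre in a three-centre trial with a locally examined imaging outcome, and the stated similarity of the centres does not reach measurement.

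Under assumed shifts of 0.25 to 0.5 SD in the analysed outcome, power in the example falls from about 85% to between 84% and 79%. If the centres do not differ, nothing is lost. If the list was not stratified, an arm gap of 10 or more at some centre has a chance of about 34% to 50%, depending on centre sizes that the article does not give. Neither systematic bias nor an inflated false-positive rate follows.

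**What to change.** 1. Include centre as a factor in the between-group models, above all for the liver-kidney echo ratio: for example, ANCOVA of the week-12 value with treatment, baseline value and centre.
2. State whether the randomisation list was stratified or blocked by centre, and report arm counts by centre.
3. Record whether the centre term was adopted before the treatment codes A, B and C were opened. If it was adopted later, report the adjusted result as a sensitivity analysis beside the named one-way test.

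The cost is two degrees of freedom among 243 patients, with little or no gain if the centres prove alike. All three steps remain possible after data lock. Permuted blocks within centre, with drug packs numbered by centre, would have been preferable at the design stage, but recruitment is complete and that option has gone.

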### Data collection and management

The Trial Steering Committee will be composed of the principal investigator (GJ) and coordinators from three centers. The committee will be responsible for revising study design, reviewing overall progress and communicating with Medical Ethics Committee per 6 months. An independent DMC will also be established by the trial steering committee. The DMC will include clinical epidemiologists, data monitors, and statisticians. No competing interest will exist. The DMC will review the efficacy and safety data according to the participants’ schedule and provide suggestions to the Trial Steering Committee on revising the study design or terminating the trial.

Clinical investigators will be responsible for the data collection during this study according to the schedule. CRFs should be filled in after every visit to guarantee the accuracy and timeliness. Data monitors from the DMC will review the CRFs each month. When a participant finishes all treatments and follow-up, the completed CRF will be verified by the coordinator. During the research process, the Trial Steering Committee will also assign research assistants every month from the Shanghai University of Traditional Chinese Medicine to solve potential problems encountered during the trial and guarantee the quality of the study execution.

In order to improve the compliance of patients to the intervention, free tests and free medical education will be provided. On the consent form, participants will be informed that they can withdraw the trial at any time and that the withdrawal decision will not interfere the regular medical care. Participants will also notice that their personal information will be de-identified throughout the trial to guarantee confidentiality. For participants who discontinue or deviate from intervention protocols, the researcher should contact the individuals, ask them for reasons, record the last time of taking medicine, and complete the evaluation items as much as possible.

### Statistical analysis

The analysis of efficacy and safety will be based on the principle of intention-to-treat (ITT), namely all randomized participants will enter the final analysis. The missing value will be filled by the method of the last observation carried forward. Data will be presented as mean with standard deviation, median with range, or number with percentage. Data analysis will use the SPSS 19.0 for Window software. All statistical inferences will be performed using a two-sided test with a statistically significant test level of *P* < 0.05 and the confidence interval of parameters will be estimated by 95% confidence interval. Differences within groups will be assessed by paired t-test, chi-square test, or Wilcoxon signed rank test according to specific variables. Differences between groups will be assessed by one-way analysis of variance or Kruskal–Wallis test based on characteristics of data. Post-hoc pairwise multiple comparisons will be performed if statistical significance is found.

No interim analysis was arranged in this trial due to a short intervention period and safety profiles of LGZG. Potential sub-group analyses will be determined based on characteristics of included participants, for instance, different categories of body mass index and different combined diseases.

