**Fig. 1 Fig1:**
[figure not shown]
*Flow chart* of the clinical study

**Table 1 Tab1:** Participant timeline

	Study phase					
	Screening	Allocation	Intervention			Follow-up
**Time point (weeks)**	**–2**	**0**	**4**	**8**	**12**	**16**
*Enrollment*						
Eligibility	**X**					
Informed consent	**X**					
**Allocation**		**X**				
*Intervention*						
SLGD			**X**	**X**	**X**	
LLGD			**X**	**X**	**X**	
Placebo			**X**	**X**	**X**	
*Assessment*						
Demographic indexes	**X**	**X**				
HOMA-IR		**X**	**X**		**X**	**X**
Hepatic function		**X**	**X**		**X**	**X**
Lipid metabolism		**X**	**X**		**X**	**X**
Glucose metabolism		**X**	**X**		**X**	**X**
Inflammation response		**X**	**X**		**X**	**X**
Liver-kidney echo ratio		**X**			**X**	
Body measurements		**X**	**X**	**X**	**X**	**X**
TCM pattern scale		**X**	**X**	**X**	**X**	**X**
SF-36		**X**			**X**	**X**
SAS		**X**			**X**	**X**
SDS		**X**			**X**	**X**
Vital signs		**X**	**X**	**X**	**X**	**X**
Blood routine test		**X**	**X**		**X**	**X**
Electrocardiograph		**X**	**X**		**X**	
AEs		**X**	**X**	**X**	**X**	**X**
Biological sample collection		**X**	**X**		**X**	**X**

*AE* adverse event, *LLGD* low dose Lingguizhugan decoction, *SLGD* standard dose Lingguizhugan decoction

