### Outcome measures

The schedule for all outcome measures is shown in Table 1. All demographic data will be determined before treatment, including the date of birth, gender, body weight, height, medication history, past medical history, smoking and drinking status, and course of disease.

The primary outcome will be the proportion of participants with at least a 1-unit decrease of HOMA-IR from baseline to treatment endpoint (week 12) [33]. Secondary outcomes will include body measurements (body weight and body mass index), hepatic function (alanine aminotransferase [ALT], aspartate transaminase [AST], gamma-glutamyl transpeptidase [GGT], and alkaline phosphatase [ALP]), lipid metabolism profiles (total cholesterol [TC], TG, low-density lipoprotein cholesterol [LDL-C], high-density lipoprotein cholesterol [HDL-C], apolipoprotein A [apoA], apolipoprotein B [apoB], and non-high-density lipoprotein cholesterol [non-HDL-C]), glucose metabolism profiles (fasting blood glucose [FPG], fasting insulin [FINS], and glycosylated hemoglobin [HbA1c]), inflammatory responses (white blood cell [WBC] counts, C-reactive protein [CRP], and inflammatory cytokines), liver-kidney echo ratio by ultrasound, and scorings of various questionnaires (TCM spleen-yang pattern scale, the MOS item short from health survey [SF-36], self-rating depressive scale [SDS], and self-rating anxiety scale [SAS]). All secondary outcomes will also be evaluated from baseline to treatment endpoint.

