### Sample size estimation

Sample size was estimated based on the clinical primary outcome. As far as we know, this is the first RCT evaluating the efficacy of LGZG versus placebo. No data are available as a reference. Therefore, based on our previous animal studies and consultation with TCM experts, we assumed that the effect size for the SLGD group is 30%, LLGD group is 15%, and placebo group is 10%. If α = 0.05 and β = 0.10, the sample size can be calculated by the following formula:
$$ \mathrm{n}=\frac{1641.4\lambda }{{\left({\sin}^{-1}\sqrt{p_{max}}-{\sin}^{-1}\sqrt{p_{min}}\right)}^2} $$

The λ is the degree of freedom, taking 12.65 in this case. The p_max_ is 30% and the p_min_ is 10%. Assuming the maximum dropout rate is 20%, 81 patients will be required for each group, with a total of 243 patients.

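### Last observation carried forward fills a missing week-12 HOMA-IR response from baseline or week 4, so the primary result depends on when patients left

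*Protocol article*

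**What the plan says.** The primary outcome (Outcome measures) is the "proportion of participants with at least a 1-unit decrease of HOMA-IR from baseline to treatment endpoint (week 12").

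The Statistical analysis section adopts intention-to-treat, "namely all randomized participants will enter the final analysis", and then gives one missing-data rule with no outcome named: "The missing value will be filled by the method of the last observation carried forward".

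Table 1 ("Participant timeline") marks HOMA-IR at weeks 0, 4, 12 and 16. Week 8 is a visit, but HOMA-IR is not marked there.

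Sample size estimation sets the scale: "Assuming the maximum dropout rate is 20%, 81 patients will be required for each group, with a total of 243 patients".

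Two other sections bear on how many values will be missing. Data collection and management asks that people who stop or deviate be contacted and evaluated as far as they can be. Concomitant treatment regulations asks the same of patients who leave because their disease progresses, and labels those cases invalid.

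**The concern.** Carrying forward a last value assumes that HOMA-IR would have stayed where it was last seen. Here that value is either the baseline or a single early reading, because nothing is measured between weeks 4 and 12. Two patients with the same unseen week-12 state are scored differently if one left in week 3 and the other in week 5. The first is a non-responder by arithmetic. The second keeps whatever was recorded at week 4. A patient who missed week 12 but returned at week 16 has a later reading that the rule does not use.

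The same mechanism reaches secondary outcomes. The liver-kidney echo ratio, SF-36, SAS and SDS have no visit between weeks 0 and 12, so a missing week-12 value is always recorded as no change.

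At stake are the primary responder rates, the differences between arms, and the precision attached to them. If leaving differs between arms in amount or timing, the rule can turn that into an apparent treatment difference.

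**Working it through.** **Inputs from the protocol.** Responder rates 30% (SLGD), 15% (LLGD) and 10% (placebo): "we assumed that the effect size for the SLGD group is 30%, LLGD group is 15%, and placebo group is 10" (per cent). 81 patients per arm. Maximum dropout 20%, so 0.20 × 81 = 16.2, about 16 missing and 65 observed per arm.

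**The plan's own figure.** The stated arcsine formula gives 1641.4 × 12.65 / (33.21 − 18.43)² = 95 per arm before dropout, and 95.1 / 0.8 = 119 after it. The stated 81 is not reproduced. This is a separate matter. I take 81 as given, and nothing below depends on how it was derived.

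**Assumptions not in the documents.** Let d be the share with no week-12 value, f the share of those who have a week-4 value, and h the week-4 response rate as a fraction of the week-12 rate. Both f and h are varied from 0 to 1. Patients who leave are assumed to have the planning response rates.

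**Recorded rate** = (1 − d) × p + d × f × h × p.

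Same dropout and timing in every arm, d = 0.20:

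| f | h | SLGD / LLGD / placebo | SLGD − placebo |
|---|---|---|---|
| 0 | any | 24 / 12 / 8% | 16 points |
| 0.5 | 0.5 | 25.5 / 12.75 / 8.5% | 17 points |
| 0.5 | 1 | 27 / 13.5 / 9% | 18 points |
| 1 | 1 | 30 / 15 / 10% | 20 points |

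Under these conditions the rule dilutes the effect or leaves it unchanged.

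**Dropout or timing differs, no true effect** (20% response in both arms, an illustrative rate):
- 20% v 10% lost, all before week 4: 0.20 × 0.80 = 16% against 0.20 × 0.90 = 18%, a false difference of 2 points.
- 20% lost in each arm, all before week 4 in one and all after week 4 in the other: 16% against up to 20% (h = 1), a false difference of up to 4 points.

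Either arm can be the one favoured, and neither case exceeds the protocol's 20% maximum.

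**Timing differs, planned effect true** (20% lost per arm, h = 1): early loss only in SLGD gives 24 − 10 = 14 points. Early loss only in placebo gives 30 − 8 = 22 points, which exceeds the true 20.

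**Power, three-arm chi-square test at 5%** (300,000 simulations):
- 81 per arm, nothing missing: 87%.
- 65 observed per arm, rates 30/15/10%: 78%.
- 81 per arm under worst-case carry-forward, rates 24/12/8%: 76%.
- 81 per arm, half of the dropouts lost before week 4: 79–82%.

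The fair comparator is 65 observed, because the dropout happens whichever method is used. Carry-forward costs about 2 points at worst.

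**Precision where week-4 values are carried** (f = 1, h = 1, so rates stay at 30% v 10%). The standard error of the difference is √[(0.30 × 0.70 + 0.10 × 0.90) / n]. With n = 81 it is √(0.30/81) = 0.061. With the 65 observed it is √(0.30/65) = 0.068. Treating the filled values as observed makes the standard error up to about 10% too small. The overstatement is less to the extent that week 4 really predicts week 12.

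**The case against.** **Fewer values may be missing.** The 20% is a planning ceiling. The protocol asks for evaluations after discontinuation, and losses after week 12 do not touch the primary outcome. This stands: every figure above is an upper bound on that account.

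**A carried baseline is non-responder imputation**, a recognised composite outcome with a valid binomial variance. This also stands, so a reader who infers that all intervals are too narrow goes too far. The precision argument applies only to carried week-4 values, at most about 16 per arm. The protocol does not present its rule as non-responder imputation, however, and it scores patients who leave after week 4 differently.

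**The power loss.** A reader might infer that carry-forward takes power from 87% to 76%. Most of that fall is the loss of data that the protocol itself allows for, so the documents do not support the inference.

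**The 20% and the 20 points.** A reader might set the 20% dropout against the 20-point effect. One is a share of patients and the other a difference in rates, so the match carries no meaning.

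**Progression.** It is tempting to say that a patient who responded at week 4 and then left because the disease progressed would count as a week-12 success. Concomitant treatment regulations calls such a case invalid, so the documents do not establish this. They leave unclear how that label fits an analysis of everyone randomized.

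**Safety data.** The carry-forward sentence follows a statement covering efficacy and safety but names no outcome. That it applies to safety is a reading, not a stated fact.

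**An unseen analysis plan** may add sensitivity analyses, and their absence here is not criticised. The point is the rule that the protocol does state.

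**Conclusion.** The point holds. Carry-forward is the only missing-data method stated, and the HOMA-IR schedule means it can bring forward only baseline or week 4. At the 20% maximum, with equal dropout and timing, the planned 20-point difference would be recorded as 16 to 20 points. With unequal dropout or timing, a false difference of 2 to 4 points is possible when there is no effect. These sizes rest on assumed dropout timing and week-4 response, which the documents do not give.

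The direction of any bias is not fixed, and nothing in the documents shows that the rule favours the active arms. The case rests on scores that depend on the time of leaving, and on carried week-4 values being counted as observed. It does not rest on power. The flaw affects the primary estimate and its interval but does not invalidate the trial, and it should be corrected.

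**What to change.** For the primary outcome, replace carry-forward with multiple imputation of week-12 HOMA-IR within arm, using baseline, week-4 and week-16 HOMA-IR and body weight. Derive responder status in each completed data set and combine by Rubin's rules. Add a sensitivity analysis that counts every missing week-12 outcome as non-response.

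For continuous outcomes with repeated visits, use a likelihood-based repeated-measures model. Report safety on observed data.

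Reconcile the invalid label in Concomitant treatment regulations with the intention-to-treat rule in Statistical analysis, so that it is clear how those patients enter the primary analysis.

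The cost is some programming and slightly wider intervals, with no new data. Trial status reports the data locked in June 2019, so the change should be declared before the first unblinding step (the release of codes A, B and C). If that has passed, report it as a deviation or as a sensitivity analysis beside the stated rule.
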